### Description of the products

Ethenox solution is obtained by mixing a pre-packaged ethanol-saline solution with 0.6 mL of enoxaparin (10,000 U/mL) to achieve 6 mL of the required ethanol content and enoxaparin concentration (enoxaparin 1000 U/mL in 40% *v*/v ethanol). The pharmacy department of the university hospital of Clermont-Ferrand will prepare the ethanol-saline solution in flasks and will send them with enoxaparin syringes every 3 months.to the study centres in boxes containing 14 treatments.

UFH lock solution is pure sodium heparinate 5000 U/mL packaged in the form of a single-use ampoule, i.e. heparin 25,000 U / 5 mL. Citrate solution at 4% is packaged in the form of a single-use ampoule, i.e. sodium citrate 4% 5 mL.

Each centre is free to choose the antiseptic solution used but cannot change it during the course of the study. The use of an antiseptic ointment at the exit-site until wounds have healed or in the event of ESI is authorized in accordance with guidelines [26]. The use of a fibrinolytic lock solution is not allowed except in the event of TC dysfunction. The use of other antimicrobial locks is not allowed and nor is that of dressings impregnated with an antibiotic or antiseptic.

### Study description

#### Screening

Patients eligible to participate in the study will be identified by a clinical research assistant in each study centre at the beginning of the study and then weekly.

#### Enrolment

Eligible patients will be recruited during a routine hemodialysis session by an investigator from centres participating in the study. The investigator will explain the study to the patient and give him/her the information form. The patients willing to participate in the study will sign the written consent form.

#### Randomization

Enrolled patients will be randomly assigned in a 1:1 ratio either to the intervention group (Ethenox) or to the control group (reference solution: UFH 5000 U/mL or citrate 4% *w*/*v* depending on the solution instilled in the patient’s TCs prior to inclusion). Random allocation will be performed by minimization using a computer algorithm. Minimization strata will be the study centre, the incident or prevalent nature of the TC and in the prevalent group the existence or not of a previous infection of the TC in place (Fig. 1).

#### Blinding

The recognisable smell of ethanol and the need to prepare the Ethenox lock solution makes it difficult to ensure the blinding of lock solutions by nurses despite the use of masks. The study will be performed single blind for the patients and the analysts.

#### Study intervention

##### TC handling protocol

TC will be handled according to the protocol established previously in each dialysis centre in compliance with the recommendations of the French Society for Hospital Hygiene [27]. In particular, the dressing of the TC must be changed systematically at least once a week or when the dressing is no longer occlusive or in the event of signs of TCI (shivering, pain caused by the catheter or fever). The use of TCs is exclusively reserved for renal replacement therapy. Outside the dialysis centre, apart from emergency procedures, it is prohibited to use TCs for the infusion of solution or for blood sampling. If this were to occur, the patient will be included only in the intent-to-treat (ITT) analysis.

##### Treatment under study

Ethenox in the intervention group and reference solutions in the control group will be used by the hemodialysis nurse as TC lock solution after each hemodialysis session with all TCs inserted in patients during the study period. After the patient is disconnected from the hemodialysis machine, the lumens of the TC will be rinsed with 20 mL of NaCl solution at 0.9%. The lock solution under study (Ethenox, UFH or Citrate 4% *w*/*v*) will be instilled slowly with a syringe into each lumen of the TC. The volume injected corresponds to the intraluminal volume of the TC branch determined at the time of inserting the TC according to its length (Canaud TC) or as inscribed on the catheter (palindrome TC). The lumens of the TC are then blocked with a sterile plug and the occlusive dressing of the TC is performed. The lock is left in place until the next hemodialysis session. The interdialytic lock (Ethenox or control) will be aspirated before connection at the start of the following hemodialysis session according to the routine procedure of the centres.

The physician in charge of the patient will suspend or discontinue the study treatment if he/she considers that the patient’s health requires it. Patients who will not be administered their study lock more than once a month will be nevertheless included in the per-protocol analysis. In the event of temporary change of dialysis centre (hospitalization, holiday, etc.) the study lock will be suspended and resumed when the patients return to their dialysis centre. These patients will be included only in the ITT analysis.

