### Study population

Eligible patients are adult (≥18 years of age) patients undergoing chronic hemodialysis in the study dialysis centres and treated with hemodialysis/haemodiafiltration via a TC inserted in a jugular vein three times a week for at least 2 weeks.

Exclusion criteria are intended use of the catheter for less than 3 months, intolerance of or hypersensitivity to ethanol, enoxaparin or UFH and citrate, previous history of type II heparin-induced thrombocytopenia, local or systemic antibiotic treatment for prevention or treatment of a TCI in the previous 2 weeks, presence of TCI in the previous 4 weeks, previous history of bacteraemia without a negative blood culture evidence of healing, TC impregnated with anti-infective agents or anticoagulants, pregnancy or risk of pregnancy (i.e. pre-menopausal woman not using a reliable method of contraception) and breastfeeding.

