### Statistical analysis

#### General consideration

The statistical unit of the primary analysis and of most secondary analyses will be the TC. When a new TC is inserted in a patient participating in the study, the new TC will be analysed for the occurrence of a TCI or TC dysfunction only from the time when the patient fulfils the eligibility criteria. This will rule out ongoing TCI or early dysfunction of the TC due to poor positioning at the time of insertion or an anatomical abnormality of the patient.

The principal analysis will be performed on the intention-to-treat principle with Stata software (version13, StataCorp, College Station, TX). The tests will be two-sided, with a type I error set at α = 0.05. Quantitative variables will be presented as mean ± SD when normally distributed (assumption of normality studied by Shapiro-Wilk test), and for non-normal distributions as median, quartiles and range. Qualitative variables will be expressed as numbers and associated percentages.

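### The per-protocol sentence on missed locks is worded in the wrong direction: read literally, it keeps poor adherers

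*Protocol article*

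**What the plan says.** All of this is in the protocol article.

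- **Planned exposure.** Under Treatment under study, the allocated solution is the "TC lock solution after each hemodialysis session with all TCs inserted in patients during the study period". Under Study population, eligible patients are "treated with hemodialysis/haemodiafiltration via a TC inserted in a jugular vein three times a week for at least 2 weeks".
- **The rule on missed locks.** Also under Treatment under study: "Patients who will not be administered their study lock more than once a month will be nevertheless included in the per-protocol analysis".
- **The sentence before it.** "The physician in charge of the patient will suspend or discontinue the study treatment if he/she considers that the patient’s health requires it".
- **The sentences after it.** They deal with a temporary change of dialysis centre, for example for a hospital stay or a holiday. The lock is suspended and later resumed, and "These patients will be included only in the ITT analysis".
- **The other route out of the per-protocol set.** TC handling protocol prohibits certain uses of the catheter outside the dialysis centre, apart from emergency procedures, and adds: "If this were to occur, the patient will be included only in the intent-to-treat (ITT) analysis".
- **Role of the per-protocol analysis.** Under General consideration: "The principal analysis will be performed on the intention-to-treat principle with Stata software". The Primary analysis and Secondary analysis sections do not mention a per-protocol analysis.

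**The concern.** A per-protocol set normally keeps patients with small departures from the assigned treatment and removes those with large ones. This sentence names the group with the large departures and says that it stays in. Nothing else in the article limits the number of missed locks, because the two ITT-only rules depend on the type of event and not on a count.

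At stake is the meaning of the per-protocol estimate. A programmer who follows the text would keep patients who were often without the study lock. A programmer who follows the presumed intent would remove them. The two sets differ, and the article does not settle which is meant. If the choice is made after the data are seen, the set is no longer prespecified.

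**Working it through.** The plan gives no figure to reproduce. The check is to read the sentence each way, convert the threshold to adherence, and compare it with the neighbouring rules.

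**1. Locks per month.** Inputs: one lock after every session (Treatment under study) and three sessions a week (Study population).

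3 × 365.25 / 7 / 12 = 13.04 lock occasions per month, or about 13.

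**2. Adherence for a given number missed.** Adherence = 1 − missed / 13.04.

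| Missed per month | Adherence |
|---|---|
| 0 | 100% |
| 1 | 92.3% |
| 2 | 84.7% |
| 3 | 77.0% |
| 6 | 54.0% |
| 12 | 8.0% |
| all | 0% |

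**3. The possible readings.** The sentence contains one negation.

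- *Reading (a): the lock is omitted more than once a month.* The patients expressly kept miss two or more locks, so their adherence is 84.7% or lower, with no lower limit.
- *Reading (b): the lock is given no more than once a month.* The patients expressly kept receive 0 or 1 of about 13 locks, so their adherence is between 0% and 1 / 13.04 = 7.7%.
- *Apparent intent: the lock is missed no more than once a month.* The patients kept have adherence of at least 92.3%. This needs a second negation, or a verb such as *miss*, and the sentence has neither.

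Both literal readings therefore keep the patients whom the apparent intent would remove.

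**4. Comparison with the neighbouring rule.** The rule on a temporary change of centre carries no count. A patient whose lock is suspended for a single session for that reason (1 of about 13, or 8%) is ITT only. Under reading (a), a patient at the home centre who misses 6 of about 13 is kept. The two rules sit in the same paragraph and pull in opposite directions.

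**5. Effect on the estimate.** If Ethenox protects only while it is in the catheter, retained time without the lock moves the per-protocol hazard ratio towards 1. The size depends on how much time is spent off the lock in each arm and on the infection risk during that time. The document gives neither, so no figure is offered.

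**The case against.** The strongest reply is that this is a drafting slip with an obvious meaning. *Nevertheless* makes sense only as a tolerance for a minor departure, and a full protocol or SAP may define the set properly. The nurse instils the lock after each session, so frequent omission is not an obvious default. The principal analysis is ITT, and neither the primary analysis nor the sample size rests on the per-protocol set.

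Much of this stands, and it limits the point. Four stronger inferences are tempting but not supported:

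- *That the sponsor meant to keep non-adherent patients.* The wording points to the contrary intent.
- *That patients who stop the lock for good are expressly kept.* This would rest only on the sentence following the one in which the physician "will suspend or discontinue the study treatment". The text does not link the two, and a monthly count fits intermittent omissions better than permanent stopping.
- *That the per-protocol result could neither support nor challenge the ITT result.* That would need substantial time off the lock, which the document does not show.
- *That a particular diluted hazard ratio can be expected.* Any such figure would only return an assumed share of time off the lock. It would also assume average control risk during that time, although suspension is tied to the patient's health.

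The reply does not remove the defect. A detail left to a later document would be no finding, but this sentence states a threshold and states it the wrong way round. A SAP would have to follow it or contradict it.

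**Conclusion.** The point holds as a wording error in an analysis-set rule. On either grammatical reading, the sentence keeps patients with poor lock adherence, while patients suspended for a temporary change of centre are excluded. The apparent intent is at most one missed lock in about 13, or about 92% adherence. The literal text covers about 85% and below on one reading, and about 8% and below on the other.

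The consequence is confined to the per-protocol analysis; the ITT result is untouched. The direction of the harm is dilution, on the assumption that the lock acts only while in place. Its size cannot be derived from the document. The conversion to adherence rests on three sessions a week throughout follow-up. The sentence should be corrected, but it is not a flaw in the primary analysis.

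**What to change.** Replace the sentence with one in the intended direction and with a denominator, for example: *patients who miss the study lock at no more than one session per month (of about 13) remain in the per-protocol analysis; patients who miss more are included only in the ITT analysis.* The sponsor should confirm that this is the intent.

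Apply the rule identically in both arms and fix the set before unblinding. Also confirm that missed locks are captured in the eCRF. The nurse's check list described under Study assessment covers signs of infection, bacteriological samples, antibiotics, line inversion and fibrinolytic treatment, but lock administration is not among the items named.

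The cost is one sentence and one check of the data collection, plus a new data item if missed locks are not yet recorded. The downside is a somewhat smaller per-protocol set, selected on adherence after randomisation, so it should be read as supportive only. The change affects only the analysis set, not how or when patients are treated.

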### Endpoints

#### Primary endpoints

The primary outcome will be time to first TCI. In the study, TCI is a composite endpoint defined by the occurrence of at least one of the three following events: definitive TCBSI, probable TCBSI or ESI. TCI diagnosis and its type (definitive or probable TCBSI or ESI) will be assessed by an endpoint adjudication committee (EAC, see Additional file 1) blinded to study arm according to predefined criteria (Tables 1 and 2).

**Table 1 Tab1:** TC infections are defined according to the definitions of the guidelines of the DIALIN^6^ network

*TC exit-site infection*	
• Purulent discharge from the exit-site *Or* • Other local signs: redness or pain at the exit-site or along the subcutaneous tunnel (tunnellitis) *And at least one of the following criteria* - Fever (> 38.2 °C) *Or* - Positive blood culture drawn from one of the two lumens of the TC following aspiration of the lock *Or* - Polymorphonuclear leucocytosis In the absence of criterion for TC-related bloodstream infection

**Table 2 Tab2:** The definition of TCBSI is specified according to K/DOQI 2006 clinical practice guidelines for vascular access^57^ which distinguishes between definitive and probable TCBSI

*Definitive TC- related bloodstream infection*	*Probable TC-related bloodstream infection*

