##### Conduct to be followed in the event of signs of TCI

In patients presenting signs of TCI, the lock studied will be maintained and patient management will be implemented according to the decision taken by the physician responsible for the patient in accordance with the practice of each centre. The diagnosis of TCI and its type will be confirmed or not a posteriori by the EAC.

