## Discussion

TC use is frequent in chronic hemodialysis patients [30, 31]. Thus, prevention of TCIs is essential. TCIs lead to systemic antibiotic administration in more than 70% of cases [29]. This contributes to an increase in the prevalence of multi-resistant pathogens. Decreasing TCI rates by the use of Ethenox solution will reduce antibiotic consumption and the emergence of multi-resistant pathogens.

TCIs are responsible for high morbidity and mortality in chronic hemodialysis patients [1]. TCBSI leads to hospitalization for 75% of patients. Mortality related to TCBSI is about 20%. The harmful effects of TCIs are also indirect. Recurrent TCIs are associated with a chronic low-grade inflammatory state [32] that is involved in the pathogenesis of protein-energy wasting syndrome. TCIs have also been associated with an increased risk of cardio-vascular events [33]. Thus, inflammation due to infection may cause accelerated atherosclerosis. Prevention of TCI is therefore of paramount importance for improving endpoints in chronic hemodialysis patients fitted with TCs.

Ethenox solution is less expensive than the other antimicrobial solutions (€3.20 for Ethenox made with enoxaparine as against €30 for taurolidine citrate) and of equal cost as citrate 4% *w*/*v* (€2.80). The price of enoxaparin will decrease once enoxaparin generics, which are already on the market in several countries, are made available in France. Several studies have estimated the cost of treating a TCBSI at about €20,000 [34]. Thus, preventing TCI could lead to a significant reduction in health expenditure.

Finally, the results of this study will help to establish with a high level of evidence national and international recommendations for the prevention of TCIs in chronic hemodialysis patients.

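### The per-protocol rule drops patients for a temporary change of dialysis centre with no exception for admissions caused by or following a catheter infection, so the set is selected on the outcome

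*Protocol article*

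**What the plan says.** Under Treatment under study, the protocol article sets the rule in two steps: "In the event of temporary change of dialysis centre (hospitalization, holiday, etc.) the study lock will be suspended", and then "These patients will be included only in the ITT analysis". The consequence applies to the whole patient, not to the time away. No exception is given for an admission due to a TCI, for an absence after the first TCI, or for a short stay.

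Just before this, the same section treats missed locks differently: "Patients who will not be administered their study lock more than once a month will be nevertheless included in the per-protocol analysis".

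Under Conduct to be followed in the event of signs of TCI, the article says: "In patients presenting signs of TCI, the lock studied will be maintained".

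The primary endpoint is time to first TCI, where a TCI is any of "definitive TCBSI, probable TCBSI or ESI" (ESI is exit-site infection). Time to first hospitalisation for TCI is a secondary endpoint. The Discussion adds: "TCBSI leads to hospitalization for 75% of patients". On the analysis set, General consideration states: "The principal analysis will be performed on the intention-to-treat principle".

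**The concern.** A per-protocol set should be defined by adherence to the assigned treatment. Here one reason for exclusion is an event that the article itself describes as a usual consequence of the more serious part of the primary endpoint. A patient who receives every lock until a bloodstream infection, and is then admitted to another centre, is removed together with the infection. A patient with a mild exit-site infection treated at the home unit stays.

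This is selection after randomisation that depends on the outcome. If Ethenox changes the rate of TCBSI, it also changes who is excluded, and by different amounts in the two arms. A gap between the ITT and per-protocol results could then come from adherence or from the exclusion rule, and a reader could not tell which.

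**Working it through.** **Inputs from the article.** Doubling of the median time to TCI (hazard ratio 0.5 under exponential survival); 90% power; "The tests will be two-sided, with a type I error set at α = 0.05"; 1:1 allocation; 400 patients; treatment for up to 12 months; median TCI-free time of 690 to 1150 days (Sample size calculation); 75% of TCBSI patients hospitalised (Discussion).

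**Assumptions, not in the article.** s is the share of first TCIs that are TCBSI. f is the share of TCBSI admissions that count as a temporary change of centre.

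**1. Reproducing the plan's sample size.**
- Freedman: events = (1.96 + 1.2816)² × (1 + 0.5)² / (1 − 0.5)² = 10.51 × 9 = 94.6, so 95.
- With a 690-day control median and 365 days per patient without dropout, the control risk is 1 − 2^(−365/690) = 0.307 and the Ethenox risk is 1 − 2^(−365/1380) = 0.168. The mean is 0.237.
- N = 95 / 0.237 ≈ 400, which matches the plan. The match holds only at the 690-day end of the range; at 1150 days the same method gives about 630. I use 95 planned events below.

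**2. TCBSI patients lost from the per-protocol set.** Share lost = 0.75 × f.
- f = 1: 75%.
- f = 2/3: 50%.
- f = 0.5: 37.5%.

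The loss is more than half only when f exceeds 2/3.

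**3. Share of all TCIs lost when every admission triggers the rule (f = 1).** Share lost = 0.75 × s; events left = 95 × (1 − 0.75s). Power at a hazard ratio of 0.5 = Φ(√events × ln 2 / 2 − 1.96). With all 95 events this formula gives 92%.

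| s (assumed) | Share of TCIs lost | Events left | Power |
|---|---|---|---|
| 0.3 | 22.5% | 74 | 84% |
| 0.5 | 37.5% | 59 | 76% |
| 0.7 | 52.5% | 45 | 64% |

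These figures count only losses through TCBSI admissions. With f = 0.5 and s = 0.5 the loss is 18.8%, leaving 77 events and 86% power.

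**4. Direction of bias.** Take a control TCI risk of 0.307, s = 0.5 and f = 1, so that the control risks are 0.1535 for TCBSI and 0.1535 for ESI. Per-protocol risk = (0.25 × TCBSI + ESI) / (1 − 0.75 × TCBSI). In the control arm this is 0.1919 / 0.8849 = 0.217.
- Ethenox halves TCBSI only: the ITT risk ratio is (0.07675 + 0.1535) / 0.307 = 0.75. The per-protocol risk is 0.1727 / 0.9424 = 0.183, a ratio of 0.183 / 0.217 ≈ 0.85.
- Ethenox halves both components: the ITT ratio is 0.50. The per-protocol risk is 0.0959 / 0.9424 = 0.102, a ratio of 0.102 / 0.217 = 0.47.

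The same rule shrinks the apparent effect in one case and enlarges it in the other.

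**The case against.** **The trigger is a change of centre, not admission.** A reader might infer that every hospitalised patient is dropped. The text does not say that: hospitalisation is an example of a change of centre, and a patient admitted but still dialysed in the home unit may not qualify. This objection stands, and it is why f is left open. The 75% is also a background figure about TCBSI, not a trial estimate and not about ESI. A reader might infer that most primary events disappear; that does not follow.

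**The missed-lock sentence is ambiguous.** It can mean that patients who miss the lock more than once a month are kept, or that no more than one miss a month is tolerated. A reader might infer that non-adherent patients stay while infected ones leave. Only the first reading supports that. What stands is that missed locks and time away are not clearly held to one standard.

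**The size depends on assumptions.** The article gives neither s nor f, nor any rate of admissions or holidays, so the total share of patients leaving the set cannot be computed. Taking s = 1 would leave 24 events and 39% power, but that supposes no exit-site infections at all. Nor can one say that the set rests mainly on mild infections: with f = 1, ESI outnumber the remaining TCBSI only if 1 − s > 0.25s, that is s < 0.8. The article also does not claim to power a per-protocol analysis.

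**ITT leads, and detail may sit elsewhere.** The statistical sections give the per-protocol set no confirmatory role. That limits the consequence. A statistical analysis plan might refine the rule, but the article does not merely leave it open: it assigns these patients to ITT only, without exception.

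**Conclusion.** The point holds in limited form. Followed as written, the per-protocol analysis excludes patients for something that the primary endpoint often causes, so it is selected on the outcome. Even if only some TCBSI admissions involve a change of centre, exclusion still depends on infection.

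Between none and three quarters of TCBSI patients could be lost with their event, depending on f. The upper end takes the article's 75% at face value and every admission as a change of centre. The table's 74 to 45 events and 84% to 64% power add the assumption that TCBSI is 30–70% of TCIs; they illustrate the loss and do not forecast it. The bias may go either way, so the per-protocol result cannot be read as a check on ITT. The ITT analysis and its sample size are not affected by this rule. The change should be made, but it does not threaten the principal conclusion.

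**What to change.** 1. Let only deviations that occur before the first TCI, and are not caused by it, affect the per-protocol analysis.
2. Count a TCI that precedes or triggers an interruption of the study lock as an event.
3. For other interruptions, keep the patient and censor at the start of the interruption. Such censoring may itself be informative, so extend the inverse-probability-of-censoring weighting, already planned under Primary analysis for catheter removal, to it as a sensitivity analysis.
4. Reword the missed-lock sentence so that its meaning is plain and one adherence standard covers both missed locks and time away.
5. Reconcile Treatment under study, where the lock is suspended when a hospitalisation changes the centre, with the section on signs of TCI, where it is maintained. The clinical rule itself is for the investigators to settle.

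The cost is wording in the analysis plan, fixed before unblinding, and some extra analysis. No more patients are needed. The sponsor must confirm that dates of lock interruption are captured: the session check list described under Study assessment covers signs of infection, samples, antibiotics, line inversion and fibrinolytics, but does not name lock administration.
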